### Data integrity and management

All collected data are recorded using case report forms which will be processed centrally at the Clinical Informatics and Data Management Unit, Department of Epidemiology and Preventive Medicine, Monash University. The hard copies of the case report forms will be stored in a locked area at each study site with secured and restricted access. The electronic data will be stored in a password protected database with secured and restricted access. All data collected will be kept strictly confidential. Data transfer will be encrypted with all data de-identified.

### Withdrawal

If participants withdraw from the study before 2 years of follow-up, the reason and date will be recorded. If the participant withdraws after a minimum of 6 months of treatment, he/she will be requested to have a second knee MRI scan and complete the questionnaires.

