### Study procedure

At screening, participants will complete questionnaires, have a knee X-ray, and undergo biochemical testing including liver function tests, creatine kinase and renal function tests, to ensure inclusion criteria are met. The study knee will be defined as the one with symptomatic OA; if both are symptomatic, the one with least severe radiographic OA (joint space narrowing) will be studied, to reduce loss to follow-up for joint replacement. After screening, study visits will be scheduled for 0 (baseline), 6, 12 and 24 months (Table 2). The same researchers, who are blinded to treatment allocation, will measure all clinical variables, administer questionnaires, monitor compliance, and record adverse events at these visits. Compliance by trial medication will be assessed by pill count. Biochemical testing will be performed at 4 weeks, and at 6, 12 and 24 months. At baseline and 24 months the index knee will be imaged on the same whole-body MRI unit.

**Table 2 Tab2:** Timetable and measures to be made

	Screening	Month 0 (baseline)	Week 4	Month 6	Month 12	Month 18	Month 24
X-ray	√						
Biochemical testing	√		√	√	√		√
Questionnaires	√	√		√	√		√
Knee VAS	√	√		√	√		√
Knee WOMAC		√		√	√		√
IPAQ		√					√
SF-36		√					√
Concomitant medications	√	√		√	√		√
Smoking		√					√
History of joint disease	√	√					√
Co-morbidities	√	√					√
Education and occupation		√					
Physical examination		√					√
Height and weight		√					√
Lower limb muscle strength		√			√		√
Knee MRI		√					√
Compliance and adverse events				√	√	√	√
Medication dispensing		√		√	√	√	

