### Sample size calculation

#### Primary outcome

Based on our previous published data, the rate of tibial cartilage volume loss in the control group was 3.0 +/− 3.0 per annum [47]. A 33 % reduction (that is, 1 %) in this rate is clinically significant since this indicates a significant reduction in structural progression of cartilage damage. Our previous work has shown that a 1 % reduction in the annual rate of cartilage volume loss over 2 years decreased the need for knee replacement surgery by 20 % over a 3-year period based on the strong association between the rate of cartilage volume loss and subsequent knee replacement [48]. With 140 participants in each arm, we will have 80 % power to detect a 30 % reduction in the rate of cartilage volume loss in the intervention group (2.0 %) compared with the control group (3.0 %), with alpha error 0.05, two-sided significance. Given our previous experience in such studies, we expect a maximum dropout rate of 20 % over 2 years. Therefore, a total of 350 participants (175 in each arm of the study) will be recruited.

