### Statistical analysis

The primary analyses will be intention-to-treat analyses of primary and secondary outcomes. Per protocol analyses (according to protocol adherence for patients who have taken all the study medication and have had all the outcome measures) will be performed as the secondary analyses. Intention-to-treat analysis will be carried out by using multiple imputation [50], provided that patients have had a baseline MRI. This analysis only requires missing data to be missing at random to be valid. Differences within a treatment group between follow-up and baseline measures will be assessed using a paired samples *t*-test. The clinical efficacy measures, that is, changes in pain and function, will also be analysed using the normalised area under the curve for difference in scores from baseline to month 24. Differences between treatment groups will be assessed using independent samples *t*-tests, ANCOVA (for continuous variables) or chi-squared tests (for dichotomous variables). Multiple linear regression for continuous endpoints or logistic regression for binary endpoints could be carried out as supplementary analyses for additional adjustment for imbalanced baseline factors. Analyses of treatment efficacy will be done by censoring participants at the time of any protocol deviation and developing a model for the probability of deviation, followed by weighted analyses using only the uncensored participants where the weights are the inverse probability of censoring. This produces estimates of treatment effect as if there were full compliance with the protocol in this trial and is far preferable to per protocol analyses based on (unweighted) observed compliance [51]. Pre-specified analyses to identify subgroups which may respond better to treatment will be examined using stratified analyses; variables include radiographic OA and co-pathology present on MRI.

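### Leavers are asked for follow-up outcomes only after 6 months of treatment, so earlier leavers enter the primary intention-to-treat analysis largely through imputation

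*Protocol article*

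**What the plan says.** The Withdrawal section of the protocol article has two sentences. The first covers everyone who leaves early: "If participants withdraw from the study before 2 years of follow-up, the reason and date will be recorded". The second adds outcome collection for some of them: "If the participant withdraws after a minimum of 6 months of treatment, he/she will be requested to have a second knee MRI scan", together with the questionnaires. The threshold is counted in months of treatment. No outcome assessment is requested of those who leave sooner.

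The visit schedule carries no such condition. Under Study procedure, "At baseline and 24 months the index knee will be imaged on the same whole-body MRI unit", and Table 2 lists the month-24 MRI and questionnaires without reference to whether tablets are still being taken.

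Under Statistical analysis, "The primary analyses will be intention-to-treat analyses of primary and secondary outcomes". The method is stated: "Intention-to-treat analysis will be carried out by using multiple imputation [50], provided that patients have had a baseline MRI". So is its assumption: "This analysis only requires missing data to be missing at random to be valid". Adherence has its own analysis: "Analyses of treatment efficacy will be done by censoring participants at the time of any protocol deviation", with inverse-probability weights.

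**The concern.** An intention-to-treat question asks what happened over 2 years to everyone randomised, whatever treatment they took. A follow-up rule that depends on time on treatment works against that. It withholds the request from the leavers with the least exposure, whose outcomes under assignment are the least likely to resemble those of participants who stayed on treatment.

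The wording also leaves a practical gap. The section speaks of leaving the study but counts time on treatment. It does not say what happens to someone who stops tablets yet would return at month 24. A site could close that person out.

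The primary estimate is what is at stake. If active-arm early leavers are imputed from participants who stayed on treatment, they may be credited with benefit they did not receive. The result then drifts toward the full-compliance effect, which the article assigns to a separate weighted analysis.

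**Working it through.** **1. The plan's own figures.** The sample size section gives a control loss of 3.0 % per year (SD 3.0), an active loss of 2.0 %, two-sided alpha 0.05, 80 % power and 140 per arm.

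- n per arm = 2 × (1.960 + 0.842)² × 3.0² / 1.0² ≈ 141.3, rounded up to 142, against 140 stated.
- Power at 140 per arm is 79.6 % (79.4 % with the noncentral t).
- For dropout, "we expect a maximum dropout rate of 20 % over 2 years": 140 / 0.80 = 175 per arm, 350 in total.

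The sample size reproduces and is not in dispute. The allowance of 35 per arm protects precision. It does not protect against bias.

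**2. What is known about an early leaver.** In Table 2, knee MRI is done at month 0 and month 24 only. WOMAC and the pain scale are first repeated at month 6. Before month 6 the only scheduled post-baseline measurement is the week-4 biochemistry. Someone who leaves before month 6 may thus have no post-baseline efficacy outcome, and the imputation rests on baseline data and on other participants.

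**3. Possible size.** Three assumptions are needed that are not in the article:

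- a share p of the active arm leaves before 6 months;
- these participants progress at the control rate of 3.0 % per year;
- they are imputed at the treated mean of 2.0 %.

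Control-arm early leavers progress at 3.0 % and are imputed at 3.0 %, so they add no bias.

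True active mean = (1 − p) × 2.0 + p × 3.0 = 2.0 + p. True difference = 3.0 − (2.0 + p) = 1.0 − p. Estimated difference = 1.0. Overstatement = 1/(1 − p) − 1.

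| p (share of the 20 % dropout) | True difference | Overstatement |
|---|---|---|
| 5 % (a quarter) | 0.95 | 5.3 % |
| 10 % (half) | 0.90 | 11.1 % |
| 15 % (three quarters) | 0.85 | 17.6 % |
| 20 % (all) | 0.80 | 25.0 % |

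Unequal early withdrawal between arms is not needed for this result. Partial reversion shrinks it: if early leavers keep half the benefit and p = 10 %, the true difference is 1.0 − 0.10 × 0.5 = 0.95, an overstatement of 5.3 %.

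**4. Which scan would help.** The primary outcome divides the change by the time between scans, and the stated coefficient of variation is 2.0–3.4 %. Taking that as per-scan error, independent between scans (an assumption), the error SD of the annualised change is √2 × CV / T:

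- at 6 months (T = 0.5): 5.7 to 9.6 % per year;
- at 24 months (T = 2): 1.4 to 2.4 % per year.

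A scan taken on leaving early is noisy and does not measure the 2-year outcome. The month-24 scan does.

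**The case against.** A reader might infer that anyone who stops tablets before 6 months is never scanned again, and that the article equates stopping treatment with leaving the study. The text does not support either reading. The Withdrawal section concerns leaving the study, and the month-24 MRI is scheduled without requiring continued treatment. A participant who stops tablets but stays in the study is still due for it. The statistical section treats incomplete medication and missing outcome measures as separate conditions in its per-protocol definition, and handles protocol deviation in its own analysis. The article is unclear on off-treatment follow-up, and a full protocol may cover it.

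The 6-month floor can also be defended as a guard against noisy exit scans, and step 4 bears this out. But that argument covers only an exit scan. It gives no reason to leave out a month-24 scan for someone willing to attend.

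It would also go too far to say that imputation cannot deal with these participants. The imputation model is not specified. Placebo data, scans from later leavers and month-24 scans from people off treatment could all inform it.

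The size is open to challenge too. The illustrated shifts of 0.05 to 0.15 points compare with a standard error of 3.0 × √(2/140) ≈ 0.36. The fix does not remove the whole shift, because some of the 20 % will refuse any follow-up. The article gives no early withdrawal rate and no evidence that it differs between arms.

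What remains is a stated rule, not an omission: among leavers, outcome collection depends on treatment exposure, which does not fit the stated primary analysis.

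**Conclusion.** The concern holds in a limited form. Participants who withdraw before 6 months of treatment are not asked for a second MRI or questionnaires, and they enter the primary analysis through missing-at-random imputation with little or no post-baseline outcome data. Without their outcomes the assumption cannot be checked in them. The likely direction, if there is bias, is toward the on-treatment effect.

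The overstatement of about 5, 11 or 18 % is an illustration. It rests on an assumed early share of 5, 10 or 15 %, full reversion to 3.0 % per year and imputation at 2.0 %. It is neither a forecast nor the gain to expect from the fix. The sample size is unaffected.

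**What to change.** In the Withdrawal section:

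- remove the 6-month treatment condition for outcome follow-up;
- state that stopping study medication is not withdrawal from the study;
- ask every participant who stops medication at any time and still consents to follow-up to attend the scheduled questionnaires and the month-24 MRI;
- state that these data are used in the intention-to-treat analysis.

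Only those who withdraw consent for follow-up would then have outcomes missing by rule.

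The change concerns data collection only. It takes one paragraph of protocol text with matching consent wording and adds no procedure, because the month-24 visit is already scheduled. The cost is some effort to retain people who are off treatment and a possibly smaller intention-to-treat effect. Trial status says recruitment was under way, so the change is best made early: scans that are not sought cannot be recovered at analysis.

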### Monitoring

The principal investigators will monitor the conduct and progress of the project at each site. The trial coordinator will visit each study site to make sure that all trial procedures are compliant with the trial protocol. The principal investigators and the research team will have regular teleconferences to ensure efficient study execution and ongoing monitoring of the study progress, with summary documents circulated after each meeting. An independent Data and Safety Monitoring Board was convened, consisting of a clinical rheumatologist, a clinical cardiologist experienced in statin use, and a biostatistician, all with clinical trial experience. They will monitor adverse events. They will meet annually or more often if severe adverse events occur, and provide a written report to the principal investigators.

## Discussion

We proposed a multicentre, randomised, double-blind, placebo-controlled trial to determine whether atorvastatin has a disease modifying effect in symptomatic knee OA by slowing the structural progression of knee OA and improving knee symptoms. If atorvastatin is proven to be effective, it will offer a novel therapeutic approach to reducing the progression of knee OA.

Oral administration of statins is an established, safe and well-tolerated treatment for the prevention of cardiovascular events [23]. Extending the potential use of statins to patients with knee OA is plausible. There is *in vitro* and *in vivo* evidence that statins may reduce the progression of OA via a number of pathways including their effects on lipid metabolism and inflammation. Statins reduce the levels of C-reactive protein and the production of inflammatory cytokines including IL-6 and IL-1β, most likely through their inhibition of NF-kB activation in monocytes or endothelial cells exposed to inflammatory stimuli [52]. Statins inhibit IL-1β induced production of matrix metalloproteinases (MMPs), and stimulate bone morphogenetic protein 2, aggrecan, and synthesis of type II collagen and cartilage matrix proteoglycan by chondrocytes [53], which is protective against cartilage damage. Atorvastatin inhibited IL-1beta-induced glycosaminoglycan release, TNF-alpha, MMP-13, and superoxide anion formation, protecting cartilage degradation following IL-1beta-stimulated cartilage in an *in vitro* OA model [54]. In animal models, statins reduce inflammatory cell infiltration and matrix-degrading enzyme expression and inhibit pro-inflammatory cytokines, thus reducing articular cartilage degeneration and the severity and progression of OA or arthritis [55–58]. In an anterior cruciate ligament transaction induced rabbit OA model, intra-articular statin injections reduced the gross morphological and histological changes in articular cartilage [55]. In a mouse model resembling human lipoprotein metabolism, atorvastatin significantly suppressed OA development [59]. In a rabbit model of early experimental OA, intra-articular application of atorvastatin showed chondroprotective effects both macroscopically and histopathologically [60].

The previous human studies [25–30] (Table 1) are all of an observational nature and thus susceptible to selection bias, information bias and confounding, and have used insensitive tools to assess disease progression. Most of these studies examined general OA without stratifying by different joints, since emerging evidence suggests different pathogenic mechanisms of OA in knee and hip joints, with the knee affected more by metabolic factors than the hip [7]. A randomised controlled trial is required to determine whether statin use affects the structural progression of knee OA.

Although OA is a disease of the whole joint, progressive articular cartilage loss is the hallmark of disease progression. Radiographic joint space narrowing is the gold standard to assess disease progression over time and has been used as the primary endpoint to examine the effect of disease modifying OA drugs in clinical trials. However, radiographic joint space narrowing provides a crude, insensitive method to assess disease progression [36]. MRI allows non-invasive direct visualisation of all joint components and direct measurement of articular cartilage, representing a sensitive method to assess OA progression. Cartilage volume has been validated by comparison with anatomical specimens [61]. It is a clinically useful measure which is inversely correlated with radiological grade of OA [41]. Cartilage volume loss is clinically significant, as it predicts important patient outcomes of pain [62] and risk of joint replacement [48]. Cartilage defects have been validated against surgically confirmed cartilage lesions and arthroscopy [63]. They are associated with knee pain [12], predict cartilage loss independent of cartilage volume [64], and predict joint replacement [49], thus providing a further assessment of cartilage health. Being the most common subchondral bone abnormality described in OA, BMLs are associated with knee pain [65], predict disease progression [66], cartilage volume loss [13] and joint replacement [14]. Thus, these MRI-assessed knee structural changes have been chosen as the primary and secondary outcome measures in this study.

In summary, knee OA is the most common form of chronic joint disorder but has no proven pharmacological treatment that reduces structural disease progression. There is evidence that both inflammation and lipid metabolism contribute to the progression of OA. The anti-inflammatory and lipid lowering effects of stains make this class of drug a potential treatment approach to slowing the progression of OA. This randomised controlled trial will provide high-quality evidence to address whether atorvastatin has a novel disease modifying effect in OA by delaying the structural and symptomatic progression of knee OA. If demonstrated to be effective, atorvastatin could be used as a novel disease modifying agent to delay the onset of end-stage OA and the need for primary joint replacement for OA and possibly revision surgery. This has major public health importance, as it would produce substantial cost savings by delaying and possibly reducing the need for joint replacement surgery, and provide marked improvements in quality of life for people with knee OA.

### Trial status

Upon submission, the OAKS study is in the process of patient recruitment.

## Abbreviations

ACR: American College of Rheumatology
BML: bone marrow lesion
HDL: high-density lipoprotein
HMG-CoA: hydroxy-methyl-glutaryl coenzyme A
IL: interleukin
IPAQ: International Physical Activity Questionnaire
LDL: low-density lipoprotein
MMP: matrix metalloproteinase
MRI: magnetic resonance imaging
OA: osteoarthritis
OAKS: Osteoarthritis of the Knee Statin
TNF: tumour necrosis factor
VAS: visual analogue scale
WOMAC: Western Ontario and McMaster Universities Osteoarthritis Index
